## Abstract

**Background:**

Patients with depression often report recurring memories of stressful events from the past (e.g. experiences of rejection, emotional or physical abuse). These distressing memories, commonly dating back to childhood, can contribute to the development and maintenance of depression through their impact on cognitive schemas. The method of *imagery rescripting (ImRs)* addresses distressing memories and the associated emotions directly: With therapeutic support, patients recall the respective memory and modify the memory during imagination in such a way that the emotional quality and meaning of the memory changes. In this randomized trial, we will assess the impact of a three-session ImRs intervention within standard cognitive behaviour therapy (CBT) for depression, comparing it to an active control intervention (imagery relaxation).

**Method:**

Sixty-six patients with MDD who are currently receiving treatment (CBT) will be randomized to either (1) the experimental condition (ImRs) or (2) the control condition (imagery relaxation). Reduction of depressive symptoms, measured by the Beck Depression Inventory (BDI-II) is the primary outcome. The BDI-II will be assessed at baseline, post-intervention, and at 4-week and 8-week follow-ups.

**Discussion:**

This study will help to clarify whether adding three ImRs sessions improves the effectiveness of CBT for depression. We outline the next steps for future research and highlight the potential of this novel intervention for depression.

Depression, characterized by low mood and diminished interest in previously rewarding activities, is a pervasive mood disorder and a global health concern (American Psychiatric Association, 2013; Ferrari et al., 2013; James et al., 2018; Whiteford et al., 2013). Despite the effectiveness of established psychological treatments like Cognitive Behavioural Therapy (CBT; Beck, 1970) in alleviating depressive symptoms, approximately 40% of patients do not respond adequately, underscoring the need for innovative interventions (Cuijpers et al., 2021; Zhdanava et al., 2021). The gap between the number of patients in treatment and treatment success points to the importance of further improving the treatment of depression.

A crucial aspect often overlooked in current psychological treatments is the presence of distressing memories, reported by about 80% of depressed patients (Brewin et al., 1996; Newby & Moulds, 2011a; Payne et al., 2019). These memories, even in the absence of traumatic events, predict depressive symptoms and persist to trouble patients who have recovered from depression (Buckman et al., 2018; Kuzminskaite et al., 2022; Nelson et al., 2017; Newby & Moulds, 2011b; Payne et al., 2019). Thus, distressing memories are not only common in depression but could also be a significant treatment target. Distressing memories are associated with unpleasant emotions such as sadness, shame, fear, or anger. While traditional CBT addresses cognitive and behavioural aspects of emotional problems, recent psychotherapy research underscores the importance of bringing the patient’s emotions into focus (Greenberg, 2010, 2017; Peluso & Freund, 2018). One technique to address both the distressing memories and the associated negative emotions is Imagery Rescripting (ImRs; Arntz & Weertman, 1999). ImRs, a therapeutic technique integrated into therapeutic approaches or used as a standalone intervention (Kip et al., 2023), addresses distressing memories in a two-step process (Arntz & Weertman, 1999). First, the individual vividly imagines the distressing memory, engaging various sensory modalities and experiencing the connected emotions. In the second step, the sequence of events is imaginatively transformed into a more desirable direction. This is achieved through the introduction of a supportive figure – such as the therapist or the patient’s adult self – who addresses the individual’s emotional needs. ImRs does not alter original memory content but aims to reduce the memory’s emotional meaning and emotional impact (Aleksic et al., 2024; Arntz, 2012; Arntz & Weertman, 1999). Arntz (2012) hypothesizes that the central mechanism of change in ImRs is the modification of maladaptive schemas, with emotional changes occurring as a by-product of this process. This perspective emphasizes the cognitive restructuring aspect of ImRs, where the reimagining of events leads to a shift in underlying belief systems, subsequently influencing emotional responses. Experimental research supports the idea that mental imagery has a profound impact on emotion (Holmes et al., 2008, 2009; Ji et al., 2016) and that ImRs reduces negative emotions and distress associated with negative memories (Çili & Stopa, 2021; Nilsson et al., 2012; Reimer & Moscovitch, 2015; Strohm et al., 2021). The positive impact of ImRs on negative emotions as well as on the distressing memories seems promising for the treatment of depression.

Despite its early recognition in CBT (Beck, 1970), the clinical applications of mental imagery within a CBT framework were relatively under-researched until recently, with pilot studies of ImRs as standalone interventions for depression demonstrating significant effects on symptom severity (Brewin et al., 2009; Ma & Lo, 2022; Pile et al., 2021; Renner & Holmes, 2018). Additionally, research has shown that engaging in mental imagery of future positive events can increase behavioural activation in individuals with major depressive disorder, further highlighting the potential of imagery-based interventions in depression treatment (Renner et al., 2017). Meta-analyses by Kip et al. (2023) and by Kroener et al. (2023) have further supported the efficacy of ImRs in treating various mental disorders associated with aversive memories, including depression, revealing large pre-post effect sizes across different disorders and highlighting its potential as a transdiagnostic intervention. Building on this evidence, a recent controlled pilot study by Kanczok et al. (2024) investigated the combined use of cognitive restructuring (CR) and ImRs compared to treatment as usual among inpatients with moderate and severe depression. The study found that patients in the intervention group (receiving CR and ImRs) achieved significantly greater improvements in depressive symptoms over time compared to the treatment-as-usual group. While these findings are promising, further research is needed to investigate the specific additional effect of using ImRs during regular cognitive behavioural therapy, particularly in outpatient settings and with larger sample sizes.

In addition to the open research questions regarding the extent to which ImRs affects depressive symptoms, there is also a lack of evidence regarding the potential mechanisms that play a role in ImRs. Studies have shown some evidence for different potential mechanisms on a cognitive level that might be responsible for the effect of ImRs: One aspect that several studies point out is the positive impact of ImRs on different aspects of a person’s self-representation (Lee & Kwon, 2013; Wild et al., 2008), self-belief (Cooper, 2011) and self-esteem (Çili et al., 2017). There are study results that indicate that the negative core beliefs associated with the distressing memories reduce in subjects treated with ImRs (Reimer & Moscovitch, 2015). Mancini and Mancini (2018) suggest that the effect of ImRs is based on a reduction of the ‘meta-emotional problem’, which is linked to a better acceptance of the negative emotions associated with the distressing memories. In the treatment of posttraumatic stress disorder (PTSD) related to traumas experienced in childhood, changes in strengths of encapsulated beliefs and distress of the index trauma preceded changes of PTSD-severity in ImRs (Rameckers et al., 2024), supporting the theory that change in emotional meaning of the memory underlies the effects of ImRs. Assmann et al. (2024) investigated the role of cognitions in the treatment of childhood-related PTSD using ImRs. Their study found that changes in trauma-related cognitions significantly mediated the relationship between ImRs and reductions in PTSD symptoms. These results highlight the critical role of cognitive processes in the effectiveness of ImRs and suggest that targeting maladaptive cognitions may be a key mechanism through which ImRs facilitates therapeutic change in PTSD. Further research is needed on the effects of ImRs on different aspects of cognition and emotion as well as on the ‘meta-emotional problem’.

Current research points to the problem that the effect of ImRs on depression has not been tested sufficiently in studies yet, especially not as an adjunct to regular cognitive behavioural therapy. Furthermore, the mechanisms of action of ImRs for depression remain unclear. This randomized controlled trial aims to expand the research on ImRs in depression. The primary objective is to evaluate the effectiveness of ImRs as an add-on to standard CBT for major depressive disorder (MDD). Patients receiving CBT in routine care are randomized to receive either three sessions of ImRs or an active control condition (imagery relaxation). We hypothesize that participants in the ImRs condition will show greater reductions in depressive symptoms from pre-intervention to post-intervention and follow-up. Although ImRs may be applicable across a range of disorders (Kip et al., 2023), we chose to focus specifically on depression in the present study for several reasons: First, the high prevalence of distressing memories among individuals with depression suggests a particularly strong clinical relevance of ImRs in this context (Brewin et al., 1996; Newby & Moulds, 2011a; Payne et al., 2019). Second, existing studies have primarily evaluated ImRs as a standalone intervention; its potential additive effect when embedded within standard CBT for depression remains largely unexplored. Third, depression continues to be among the most prevalent and burdensome mental health conditions, underlining the need for innovative adjunctive treatments. Given these considerations, we see depression as a particularly meaningful starting point for examining the clinical utility of ImRs. Importantly, comorbidities are not excluded in our study, reflecting the complex presentations often encountered in routine clinical practice. Secondary objectives of this trial include examining changes in associated psychological variables (e.g., repetitive negative thinking, emotional capabilities, self-compassion, self-esteem). In addition, exploratory analyses will investigate potential mechanisms underlying the effects of ImRs.

## Method

### Design

The study is a two-arm randomized controlled trial with one active intervention condition (Imagery Rescripting, ImRs) and one active control condition (imagery relaxation). Participants in both conditions are invited to complete questionnaires at baseline session (Session 1), Weeks 1-3 after baseline (intervention Sessions 1-3) and at post and Follow-up 1 and 2 (Week 1, 4 and 8 after the last session). The medical ethics committee of the University of Freiburg has approved the study (Approval number: 22-1518-S2). The study is pre-registered at the German Clinical Trials Register https://drks.de/search/de/trial/DRKS00031495.

### Participants

Inclusion criteria are (a) meeting the diagnostic criteria for a current major depressive disorder (MDD), as assessed with a SCID-5-CV interview (patients with comorbid disorders are eligible to participate), (b) age 18 years or older, (c) sufficient proficiency of German language to complete questionnaires. Patients are excluded from participation if they are at high risk of suicidality, defined as the presence of acute suicidal ideation with concrete plans or intent. This is assessed during the standard intake procedure at the outpatient clinic where the study is conducted. Diagnostic information is based on the initial clinical interview (SCID) conducted by the therapist at the outpatient clinic; no additional study-specific diagnostic assessment will be conducted. Participants are informed about the study at the beginning of their treatment but may enrol at any point during their ongoing CBT. The number of standard CBT sessions completed at study entry will be documented and reported. It is important to note that CBT is delivered as part of routine care in the outpatient clinic and is not part of the experimental study protocol. No efforts are made to standardize or influence the content, structure, or dose of the ongoing CBT. However, information on the number of CBT sessions and the use of imagery techniques during therapy will be collected post-hoc via therapist questionnaires.

### Sample Size

Previous research has demonstrated the effectiveness of Imagery Rescripting (ImRs) in treating various mental disorders, with large effect sizes reported when compared to inactive control conditions (Morina et al., 2017). Ma and Lo (2022) conducted a randomized controlled trial comparing ImRs to cognitive restructuring (CR) in depression treatment. Their findings revealed that both ImRs and CR led to significant reductions in depressive symptoms, with medium to large effect sizes observed. In the present study, we aim to build on these findings by comparing ImRs to an active control condition (relaxation) in the context of ongoing Cognitive Behavioural Therapy (CBT) for depression. Since both study arms receive standard CBT and the control condition is active rather than passive, we expect smaller between-group differences than in previous trials. Specifically, we anticipate moderate differences in the reduction of depressive symptoms between the two interventions. To determine the required sample size, we conducted a simulation-based power analysis using the simr package in R. The analysis was based on a linear mixed-effects model that reflects the longitudinal structure of the study, including four repeated measurement points and a random intercept for each participant. Assuming a moderate group × time interaction effect (β = 0.25) at the final follow-up (FU2), the simulation indicated that a total sample size of approximately 60–70 participants would yield a statistical power of 85–90%. To account for potential dropouts while keeping the study feasible in terms of recruitment and implementation effort, we planned a total sample size of 66 participants with equal allocation to both conditions. This sample size is expected to be sufficient to detect moderate effects over time.

### Recruitment

Eligible potential participants will receive written study information from their therapist in the outpatient clinic. If they are interested in participating, they are asked to return a consent form to their therapist, giving permission to be contacted by the research team. A member of the research team will then contact the patient to discuss the study, clarify any questions and see if the patient is interested in participating in the study. If interested, an appointment for the initial session (introductory session) will be scheduled. Informed consent for study participation will be signed at the introductory session.

### Therapists

Study therapists will be four graduated psychologists in an advanced stage of clinical training to become fully licensed psychotherapists who are working at the outpatient treatment center of the University of Freiburg. Before the start of the study, study therapists received 15 hours of training in the ImRs procedure by [name] and training in the imagery relaxation procedure by [name]. Clinical supervision meetings are planned on a regular basis throughout the study.

### Introduction Session (Baseline)

Prior to the start of the study’s therapeutic intervention, participants will complete an online baseline assessment. Subsequently, an initial 60-minute introductory session will be scheduled with each participant. In the introductory session, the participants will get to know their study therapist and distressing memories will be identified using a semi-structured interview based on the work of previous studies (Ma & Lo, 2022; Patel et al., 2007). There will be no restriction on the timeframe where the memory originated as previous work suggests that ImRs can effectively be applied to “older” childhood memories as well as more recent memories. Participants will be asked to recall three distressing memories and will be asked about the content of each memory, their age at the time when the event occurred and the context in which the event occurred. Core beliefs associated with the memory will be assessed by using a standardized protocol. The specific emotions and the current distress caused by the core beliefs will be assessed as well.

### Randomization

After the introduction session, patients will be randomized into one of the two conditions using a computer script performing block randomization (1:1, block size = 6). Randomization will be done by a researcher who is not involved in the study sessions. After the randomization, the patients will be sent a video explanation in which their study therapist explains what is going to happen in the respective condition. To ensure consistency and standardization in how each condition is introduced, participants receive a brief video following randomization in which their assigned study therapist explains the rationale, structure, and expectations of the respective intervention. These videos aim to enhance transparency, facilitate engagement, and reduce time needed for explanation during the first session, thereby allowing more time for therapeutic work.

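### The fixed, published block size of 6 lets anyone who has tracked the whole sequence be certain of some allocations, though a therapist who sees only their own patients gains almost nothing; undisclosed varying block sizes would remove most of that certainty

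*Protocol article*

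**What the plan says.** The Randomization section specifies "block randomization (1:1, block size = 6" and describes no varying sizes, strata or separate lists. It gives the timing, "After the introduction session, patients will be randomized into one of the two conditions", and a safeguard: "Randomization will be done by a researcher who is not involved in the study sessions". The assigned study therapist then introduces the allocated condition by video.

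Two things happen before allocation. Under Recruitment, "Informed consent for study participation will be signed at the introductory session". Under Introduction Session (Baseline), "participants will get to know their study therapist and distressing memories will be identified using a semi-structured interview"; core beliefs, the related emotions and current distress are assessed there too. The same section places the online baseline assessment before this session.

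Under Therapists, "Study therapists will be four graduated psychologists", with regular supervision meetings. Under Sample Size, "we planned a total sample size of 66 participants with equal allocation to both conditions". The Secondary Outcomes section includes 0–100 ratings of the core beliefs, emotions and memories identified at the baseline session.

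**The concern.** Using a researcher outside the sessions to randomise hides the list. It does not hide what past allocations imply. In a 1:1 block of 6, once one arm has used its three places, every remaining place belongs to the other arm. Therapists deliver the arm, so they learn past allocations as the trial proceeds, and the block size is in print.

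Someone who could anticipate the next allocation might, without intending to, influence who is brought to the introductory session next, how consent is discussed, or how memories and core beliefs are drawn out. That material anchors some of the secondary ratings, and the Exploratory Analyses section treats secondary outcomes as candidate mediators. What is at stake is comparability of the arms at entry and on those ratings.

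**Working it through.** The article gives no predictability figure to reproduce, so the check starts from the stated design.

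**Inputs.** Block of 6 with 3 + 3 places (Randomization); 66 patients, hence 66/6 = 11 complete blocks and 33 per arm (Sample Size); 4 study therapists (Therapists). Assumed, because the article does not say: one list, and an observer who knows where each block starts.

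**1. Observer who knows every earlier allocation.** There are C(6,3) = 20 equally likely blocks. An allocation is certain when one arm has already used its three places.
- 4th place: the first three all went to one arm, 2/20 = 10%.
- 5th place: the last two places belong to the same arm, 2 × C(4,1)/20 = 8/20 = 40%.
- 6th place: always, 100%.
- Per block: 0.10 + 0.40 + 1.00 = 1.5, and 1.5/6 = 25%. The general formula for blocks of 2m, 1/(m + 1), gives 1/4 for m = 3.
- Over 11 blocks: 11 × 1.5 = 16.5 certain allocations expected. Each block has between 1 and 3, so the possible range is 11 to 33.

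**2. Best guess by the same observer**, always choosing the arm with more places left. Expected correct guesses per block are m + 2^(2m−1)/C(2m,m) − 1/2 = 3 + 32/20 − 0.5 = 4.1. The rate is 4.1/6 = 68.3%, about 45 of 66, against 50% by chance.

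**3. Therapist who sees only their own patients**, with patients assigned to the four therapists at random. Certainty now also requires that the same therapist treated all three patients who filled the exhausted arm, with probability (1/4)³ = 1/64. So 25%/64 = 0.39%. Simulation of 20,000 blocks gave 0.36%. Either way it is about 0.4%.

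**4. Randomly varying block sizes**, with an observer who sees all earlier allocations and knows the set of sizes but not their order (simulated sequences of 66).
- Sizes 4 and 6: about 5.7% certain, best guess about 69%.
- Sizes 4, 6 and 8: about 2.4% certain, which is 0.024 × 66 = 1.6 allocations; best guess about 68%.

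**5. What foreknowledge could touch.** The BDI-II is self-report (Primary Outcome), and the online baseline assessment precedes the introductory session, so that score is already fixed. Consent and the memory, emotion and core-belief material are obtained at the session and before allocation, so they are exposed.

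**The case against.** Fixed blocks with an independent allocator are a conventional choice, and nothing here is contradictory or miscalculated. The 25% belongs to an observer whom the article does not describe: someone with all four therapists' allocations in order, plus the block boundaries. Supervision meetings provide an occasion for sharing, but that arms are tallied there is conjecture. The single list is also inferred, from silence in a condensed article. Patients are first approached by their routine therapist, who is not the study therapist, and no passage says that whoever arranges the appointment knows past allocations. Core beliefs are assessed with a standardised protocol, most candidate mediators are questionnaires, and secondary results are declared exploratory.

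Most of this stands, and it limits the size of the point. It does not remove it: the block size is stated and public, therapists do learn the arms, and the independent allocator does not prevent deduction. Nor would separate lists per therapist help. Each therapist alone could then be certain of 25% of allocations within complete blocks.

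A reader might infer that every study therapist knows a quarter of the upcoming allocations, that concealment has failed, or that the primary baseline is compromised. The documents support none of these. A lone therapist is certain for about 0.4%, no passage suggests that prediction has occurred, and the BDI-II baseline precedes the session.

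**Conclusion.** The point holds as a minor, inexpensive improvement. With a fixed, published block of 6, an observer of the full sequence is certain of 25% of allocations (16.5 of 66 expected) and guesses 68% correctly. This rests on pooled or centrally known allocations, known block boundaries and a single list, none of which the article states. Without pooling, certainty falls to about 0.4%. That the study therapist conducts the memory interview is the natural reading of a passage worded in the passive.

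The exposure is confined to enrolment and consent and to the therapist-elicited memory, emotion and core-belief baseline. Varying block sizes would remove most of the certainty. They would not make the sequence unguessable.

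**What to change.** For any patients still to be randomised, have the script complete the current block and then draw block sizes at random, for example from 4, 6 and 8. Withhold the new sizes from therapists and from public documents until recruitment ends. Record the date and the sequence position of the change.

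The costs are a small edit to the script, a documented protocol change with any ethics notification it requires, and possibly slightly unequal arms. With a single list of 66 and blocks of up to 8, the worst case is stopping halfway through a block of 8 with all four allocations in one arm, giving 35 and 31. That keeps 4 × 35 × 31/66² = 4340/4356 = 99.6% of the efficiency of an even split. The change does nothing for patients already randomised, and the article does not say how many remain.
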